# A multimodal and multidisciplinary program to prevent loss of mobility in patients aged over 70 years: study protocol of a multicenter cluster randomized study in primary care (the PRISME-3P study)

**DOI:** 10.1186/s12877-019-1059-5

**Published:** 2019-02-19

**Keywords:** Mobility, Exercise, Nutrition, Primary care, Prevention, Elderly patients

## Abstract

**Background:**

Reduced mobility is the first sign of functional decline and can lead to dependency in elderly people. Screening for the risk of mobility limitation in this population is an important public health issue to prevent further disabilities. Despite the current lack of guidelines, primary care healthcare providers may have a central role to play in this type of screening. Multi-domain physical exercise interventions in older persons have shown some efficacy/effectiveness on frailty status, yet, to the best of our knowledge, no published study has focused on patients screened in primary care.

**Method:**

The PRISME-3P study is a national, interventional, multicenter, cluster randomized trial. Patients over 70 years of age will be systematically screened by their general practitioner (GP) on the basis of clinical criteria of mobility limitation. To avoid contamination bias, the unit of randomization will be the GP practice. In the intervention group, patients will consult a geriatrician and a dietician, and will receive a physical training program from a personal trainer who will demonstrate the exercises and provide follow-up coaching. The control group will receive standard care. The primary outcome will be the change in Short Physical Performance Battery (SPPB) scores between inclusion and 6-months follow-up.

**Discussion:**

We expect an improvement of the SPPB between inclusion and 6 months of follow-up.

**Trial registration:**

This study is registered in ClinicalTrials.gov (NCT02847871, 27 July 2016).

## Background

Senior citizens are particularly exposed to the risk of dependency or functional disabilities, which represent in industrial countries a large proportion of current healthcare costs. It is also a major concern for the future considering current demographics as, although life expectancy continues to increase, life expectancy without disability tends to remain stable, and therefore the burden of disability in older people is set to increase [1, 2].

Disease, cellular aging, musculoskeletal changes, and undernutrition all contribute to decrease muscle mass which leads to sarcopenia in older adults [3, 4]. Loss of muscle mass also causes a reduced muscle strength and a decrease of maximal oxygen uptake [5]; this ultimately leads to a mobility limitation [6] and a vicious circle is established as this in turn leads to loss of muscle mass [7]. Mobility limitation is common in older adults, almost 30% in those aged over 65 years [8, 9], and the most frequently used method in the literature to measure this has been the ability to rise from a chair, walking speed, or capacity to walk 400 m [10, 11]. It is predictive of dependence and the first sign of functional decline [10, 12], which increases the likelihood of depression [13], risk of falls and fractures [14], institutionalization [15] and mortality [16], and lowers quality of life. Mobility limitation is also considered as part of the definition of frailty. For example, Fried et al. have defined frailty as a clinical syndrome in which three or more of the following criteria are present: unintentional weight loss (10 lbs. in past year), self-reported exhaustion, weakness (grip strength), slow walking speed and low physical activity [7].

To preserve muscle strength, non-pharmacological interventions promoting physical exercise or improving nutrition could be important. For instance, physical exercise is reported to preserve muscle quality and strength, but also help prevent dependency [17, 18]. Furthermore, a nutritional approach with qualitative (e.g. sufficient protein intake) and quantitative (e.g. sufficient calorie intake) nutritional factors and a higher dietary intake macro and micronutrients such as antioxidants contributes to preserve physical performance and strength [19]. Several studies have found evidence of a synergy between adapted physical activities and dietary advice to prevent mobility impairment and decrease in functional status [17, 20–24].

The systematic detection of physical impairment to be able to intervene in the negative vicious circle towards dependency is an important public health goal. Screening and prevention are 2 of the core tasks of GPs, which are often the first medical contact with older patients. There is, however, no guideline or recommendation to screen the risk of mobility limitation in older adults in primary care [25]. Mobility assessment in clinical general practice should be performed using simple, easy, and quick tools. Several tools have been developed to detect loss of mobility; identifying functional complaints in patients with mobility difficulties has proven to be a valid screening tool for detecting subsequent loss of mobility [11, 26, 27].

The aim of this study is to assess the benefits of a multimodal intervention for older adults with complaints of reduced mobility, screened systematically in primary care. The main objective of this study will be to evaluate between the control and intervention groups change in mobility and muscular force at 6 and 12 months of follow-up, evaluate physical performance, nutritional status, quality of life, and autonomy.

## Methods

### Study design

PRISME-3P is a national, multicenter, and cluster randomized trial conducted in France (Fig. 1). GPs will be randomly assigned to the intervention group or to the control group. Recruitment and inclusion will be performed by GPs and the intervention will take place at the hospital and home of the patient. The planned inclusion period is 24 months with 12 months follow-up.

**Fig. 1 Fig1:**
[figure not shown]
Design of the PRISME 3P randomized controlled trial

In both groups, GPs will perform a consultation for inclusion at baseline and two evaluations at 6 and 12 months thereafter. In the intervention group, an initial blood test will be performed (blood cell count, CRP, pre-albuminemia, and albuminemia). Follow-up will include two visits to the allocated study hospital outpatient clinic (within 2 weeks and at 3 months from inclusion) and 3 visits to the GP (at 3, 6, and 12 months from inclusion). All data collected will be notified by the GPS on the case report form (CRF).

### Identification of areas of recruitment

First, we have searched for hospital that could participate in the study (having a geriatric unit with a dietician). We have invited 8 geriatric units to participate. Second, we have contacted the university general practice department of each hospital areas, i.e. Lyon (Lyon, Villefranche-sur-Saône, Bourg-en-Bresse, Annemasse), Nantes (Nantes), Saint-Etienne (Saint Etienne) and Nice (Menton). In each department a coordinator will be designated with responsibility to recruit GPs near the hospital.

### Recruitment and randomization of GPs

A total of 60 GPs will be recruited in 8 areas of France (6 in Nantes, 6 in Dijon, 19 in Lyon, 8 in Villefranche-sur-Saône, 5 in Bourg-en-Bresse, 5 in Annemasse, 6 in Saint-Etienne, and 5 in Menton). They will be assigned to the intervention group or to the control group using the survey select procedure of SAS® (SAS Institute Inc., Cary, NC, USA). The sampling will be stratified on the referring geriatric center (i.e. city). GPs working in the same practice will be considered as a unique sampling unit to avoid risk of contamination. Each collaborating university general practice department will organize training for the screening and assessment of patients required by the study protocol, including the provision of information on the eligibility criteria and study organization.

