### Sample size calculation

The inclusion of 28 GPs per arm will provide a power of 80% to detect a difference of 0.8 points in SPPB score change between arms (1.2 points increase in the control group, versus 2 points in the intervention group), with 5 patients for each GP, an intra-cluster correlation coefficient of 0.15, and with a standard deviation of inter-individual variability of 1.7. Accounting for loss to follow-up, it is planned to randomize 30 GPs in each group, giving a total of 60 GPs and 300 patients (5 patients for each GP). The power of the study was calculated using the method described by Donner and Klar [40] and with the package CRTsize in the R program, version 3.3.1 (R foundation, Vienna, Austria).

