### Statistical analyses

The patient characteristics at inclusion will be described according to each group (intervention and control groups). A summary table will be provided in order to ensure the homogeneity of the prognostic factor distributions according to the groups. A second summary table of clusters (GPs) will also be provided. The method and the presentation of the results will be according to the guidelines for cluster trials [41].

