#### Primary outcome

All analyses of the primary outcome will be performed on the intent-to-treat population. The distribution of the primary outcome (difference in SPPB scores between inclusion and 6-month visits) will be described and presented for the two groups (graphical representation, e.g. boxplot). The primary outcome will be analyzed using a multiple linear regression model. When the conditions for application of the linear model are not respected (normality of residuals, independently distributed residuals…), a transformation (logarithmic or even Box-Cox, quantile, or z-score) of the SPPB score will be considered.

The main analysis of the primary outcome will be adjusted on the center using a mixed effect linear model with a random GP effect, and as fixed effects: an intervention effect (the control group as reference), a period effect (the inclusion as reference), and an interaction between treatment and period. This model will also be adjusted on the age at inclusion. An interaction between the SPPB at inclusion and intervention will be added to the model to test whether the treatment effect is different for patients with lower vs. higher level of SPPB score at inclusion. *P*-values and 95% confidence intervals of the fixed effects will be provided. Another analysis using the SPPB score as independent variable in a longitudinal mixed effect linear model will also be considered.

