### Discussion of the study design

The study will be randomized and multicenter, and will investigate the effect of a specific clinical pathway with both the effects of the intervention and, simultaneously, the implementation of the program in current practice conditions, across various areas of France. Rather than an individual randomization, a cluster design was chosen in order to limit the risk of contamination, but also for reasons of feasibility and ethics; it would have been difficult to justify why two different patients in the same practice would not have access to the same management. Likewise, we chose to stratify randomization to ensure that GPs working in the same practice would be randomized to the same group. The high number of clusters (60 in total) and low number of patients within each cluster should help reduce the risk of bias due to intra-cluster correlation.

Despite the cluster design, the effects of the intervention will be determined individually. An open-label design is necessary given the nature of the intervention. The effects of the intervention will be evaluated using an objective outcome, the SPPB, which has shown to be reproducible [29, 39]. An SPPB score below 10 is predictive of all-cause mortality [42] and reveals a weakness of lower extremity function and higher mobility disabilities [43]. Clinically, an improvement of one point in the SPPB score is associated with substantial and clinically relevant changes in physical performance [44]. SPPB is a reliable tool to screen for patients likely to benefit from a physical exercise program [41] and it is generally considered as a valid predictive tool to assess physical performance and predict risk of mobility loss [11, 39, 42]. The GPs will screen systematically each consecutive patient over 70 years of age to limit selection bias. Furthermore, they will note each refusal to participate in order to evaluate the acceptability of the program from the patients’ perspective.

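### Practices are allocated, but the primary model, the power calculation and the cluster count treat the GP as the independent unit, so type I error and the 80% power are not assured where GPs share a practice

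*Protocol article*

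**What the plan says.** All places are in the protocol article.

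**The practice as the allocated unit.** The Abstract (Method) says that "the unit of randomization will be the GP practice". Recruitment and randomization of GPs says that "GPs working in the same practice will be considered as a unique sampling unit to avoid risk of contamination". Discussion of the study design adds that "we chose to stratify randomization to ensure that GPs working in the same practice would be randomized to the same group". That sentence credits stratification, although the recruitment section stratifies on the referring geriatric center and keeps a practice together through the sampling unit.

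**The GP as the unit.** Study design says "GPs will be randomly assigned to the intervention group or to the control group". Sample size calculation says "The inclusion of 28 GPs per arm will provide a power of 80" percent, with 5 patients per GP, an intra-cluster correlation of 0.15 and an SD of 1.7, raised to 30 GPs per arm for loss to follow-up. Statistical analyses announces: "A second summary table of clusters (GPs) will also be provided". The main analysis of the primary outcome is adjusted for center and fitted "using a mixed effect linear model with a random GP effect". Discussion of the study design relies on "The high number of clusters (60 in total) and low number of patients within each cluster", and 60 is exactly the number of GPs to be recruited.

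No section gives a practice effect, a number of practices, or a correlation between patients of different GPs in one practice.

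**The concern.** Two GPs in one practice always receive the same arm, so they are not two independent replicates of the allocation. The random GP effect covers the likeness of patients under one GP. It treats GPs of the same practice as independent and so omits any covariance between them. If that covariance is positive, the standard error of the intervention effect is too small, and the primary test rejects a true null hypothesis more often than its nominal level. The number of independent units behind the power figure would also be smaller than stated. Adjustment for center does not repair this: center is the city stratum, and both arms lie within it.

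This is not a detail left open for an analysis plan. The article names the random effect and the number of clusters, and both sit below the level at which it says allocation takes place.

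**Working it through.** **Inputs from Sample size calculation.** Difference 0.8 points, m = 5 patients per GP, ICC 0.15, SD 1.7, 28 GPs per arm. Alpha is not stated; two-sided 0.05 is assumed, in line with the planned 95% confidence intervals.

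**Step 1: reproduce the 28.** The design effect is DE = 1 + (5 − 1) × 0.15 = 1.60. GPs per arm: k = 2 × V × (1.960 + 0.842)² × DE / (5 × 0.8²), where V is the total variance.
- 1.7 as total SD: V = 2.89, k = 22.7, so 23 (24 with t quantiles). With 28 GPs, power is 86.4% by t (87.5% by normal approximation).
- 1.7 as within-cluster SD: V = 2.89 / 0.85 = 3.40, k = 26.7, so 27 (27.7, so 28, with t quantiles). With 28 GPs, power is 80.5% by t (81.8% by normal approximation).

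The stated 28 at 80% is reproduced only by the second reading. That is back-fitting; the article does not say which SD is meant.

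**Step 2: allow for shared practices.** Let a be the mean number of GPs per practice (practices taken as equal in size) and r the correlation between patients of different GPs in one practice. Neither is given. Assumed ranges are a = 1.25 to 2 and r = 0.05 to 0.15. At r = 0.15, patients of different GPs are as alike as patients of one GP.

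DE = 1.60 + 5 × (a − 1) × r. If instead a share f of GPs is in pairs and the rest are single, DE = 1.60 + 5 × f × r.

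**Step 3: type I error of the GP-level test.** The true standard error exceeds the model's by √(DE / 1.60), and type I error ≈ 2 × [1 − Φ(1.96 / √(DE / 1.60))].

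| GPs in pairs | r = 0.05 | r = 0.10 | r = 0.15 |
|---|---|---|---|
| Half | 5.9% | 6.8% | 7.8% |
| All | 6.8% | 8.7% | 10.6% |

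Example, all paired and r = 0.15: DE = 1.60 + 0.75 = 2.35, ratio √(2.35 / 1.60) = 1.21, type I error 10.6%. Simulated t tests on GP means agree (10.4–11.1% in that case), while t tests on practice means stay near 5%.

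**Step 4: power of a test at practice level.** SE = √(2 × V × DE / 140), with 140 = 28 × 5 patients per arm, and t quantiles on 2 × (28/a − 1) degrees of freedom.

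| SD reading | r | a = 1.25 | a = 1.5 | a = 2 |
|---|---|---|---|---|
| Within-cluster | 0.05 | 79% | 77% | 73% |
| Within-cluster | 0.15 | 76% | 71% | 63% |
| Total | 0.05 | 85% | 83% | 80% |
| Total | 0.15 | 82% | 78% | 70% |

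Example, within-cluster, a = 2, r = 0.15: SE = √(2 × 3.40 × 2.35 / 140) = 0.338, 0.8 / 0.338 = 2.37, power 62.5% on 26 degrees of freedom.

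**Step 5: when 80% is lost (normal approximation, pairs, 28 per arm).** With the within-cluster SD, power falls below 80% once about 11% (r = 0.15) to 32% (r = 0.05) of GPs are paired. With the total SD, that takes about 50% (r = 0.15) or 75% (r = 0.10), and at r = 0.05 it does not happen with pairs.

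**The case against.** The strongest reply is that sharing may be rare and the practice-level correlation small. The recruitment sentence applies only where GPs share a practice, and no section says how many do. The SPPB is to be measured by the same GP where possible, so rater effects sit at GP level and are modelled. The intervention is delivered by hospital staff and at home, intervention GPs are not directly involved in it, and the hospital effect is covered by the center adjustment. Training is run by the university departments, so it is not specific to a practice. All of this stands, and it makes the upper end of the assumed correlation harder to support. It limits the size of the problem but does not remove the mismatch: the protocol thought within-practice contamination likely enough to shape the allocation.

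A reader might infer that 80% power is lost wherever GPs share a practice, or that there are certainly fewer than 60 independent units. The article supports neither. With 1.7 as the total SD, 28 GPs carry a reserve, and 80% survives moderate sharing. If every practice supplies one GP, 60 is correct.

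Nor does the GP model discard between-practice variance. The GP variance absorbs it, and only the covariance between GPs of one practice is missing. The GP-level test also keeps most of its nominal power (simulated at about 82–85% with all GPs paired, 28 per arm, total SD). Its fault is the inflated error rate, and the power loss appears once the test is made valid.

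**Conclusion.** The mismatch between the allocated unit and the analysed unit is in the text, and it affects the primary analysis. Its consequence is conditional on two things: some practices contribute two or more GPs, and their patients' SPPB changes are positively correlated beyond the GP.

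Under the assumed ranges, type I error is roughly 6–11% for half to all GPs in pairs. The 80% power is then not assured: about 63–79% on the SD reading that reproduces the 28, and about 70–85% on the other. These figures rest on two-sided alpha of 0.05, 28 GPs per arm with 5 patients each, and practices of equal size in the power table. The two further GPs per arm are meant to cover loss to follow-up and are not counted as a reserve.

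**What to change.** - In the primary model and the between-arm secondary models, add a random practice effect, with GP nested within practice where GPs share one, and base inference on the number of practices.
- Make the Abstract, Study design, Recruitment and randomization of GPs, Sample size calculation, Statistical analyses (including the primary outcome model) and Discussion of the study design agree on what the cluster is. Replace the count of 60 clusters with the number of practices randomised, and tabulate practices as well as GPs.
- Restate the power for that number of practices and their mean size, as a range over the practice-level correlation. State alpha, and have the sponsor say which SD the 1.7 is.

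The analyses within the intervention arm under Secondary outcomes compare no randomised groups, so the allocation argument does not require a change there.

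The cost is model wording and a possibly less favourable power figure. No extra patients are needed, and the change is harmless if no practice turns out to be shared.

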### Participants

All subjects aged over 70 years old will be eligible except patients with functional or locomotor disabilities, a life expectancy less than 6 months, a progressive chronic disease affecting participation in the program, or a MMSE< 20.

For each consecutive patient over 70 years of age without exclusion criteria, GPs will screen patients with medical interview to detect 2 or more inclusion criteria described in Table 1. These criteria are partly derived from the sarc-f screening tool for sarcopenia [28].

**Table 1 Tab1:** Summary of eligibility, inclusion, non-inclusion and exclusion criteria

Eligibility criteria	Inclusion criteria	Exclusion criteria
Difficulty lifting packages over 4.5 Kg	Age > 70	Patient refusal to participate to the study
Difficulty rising from low seats without help of arms	SPPB <10	Functional or locomotor disabilities
Difficulty climbing less than 10 steps of stairs	≥ 2 eligibility criteria	Life expectancy less than 6 months
Difficulty moving or reduced walking speed		A chronic disease affecting participation to the program
Difficulty walking over 400 m without break		MMSE< 20
Walking time less than 1 hour per week		
Feeling of exhaustion during domestic activity		
> 2 falls during the last year		
Involuntary weight loss (> 5% in 1 month or > 10% in 6 months)		

In the presence of 2 or more inclusion criteria, GPs will assess the patient using the Short Physical Performance Battery (SPPB) [29]. In the event of a SPPB score < 10 (out of 12), patients will be given 9 questionnaires grouped in a unique folder: Activity Scale for the Elderly (PASE) [30], weekly sedentary time inspired by Gardiner [31], Activity of daily living scale (ADL), Instrumental activities of daily living scale (IADL) [32], SF-12 scale [33], Mini-Nutritional Assessment (MNA) [34], EPICES score *(Evaluation de la précarité et des inégalités de santé dans les centres de santé (in French))* [35, 36], Charlson index [37], Geriatric Depression Scale (GDS) [38] (Table 2) that measure their autonomy, nutrition and physical activity, and will be proposed another medical appointment for inclusion in the study. If a patient refuses to participate in the study, this will be noted in the CRF.

**Table 2 Tab2:** List of questionnaires

List of questionnaires	
Physical activity	Activity Scale for the Elderly (PASE) [30]
	Weekly sedentary time inspired by Gardiner [31]
Autonomy	Activity of Daily Living scale (ADL)
	Instrumental Activities of Daily Living scale (IADL) [32]
Quality of life	SF-12 scale [33]
Nutrition	Mini-Nutritional Assessment (MNA) [34]
Patient’s social environment	EPICES score [35, 36]
Comorbidities	Charlson index [37]
Depression symptoms	Geriatric Depression Scale (GDS) [38]

